### Exclusion criteria

mean arterial pressure <60 mmHg despite infusion of fluids and vasoactive drugsratio of arterial-to-inspired oxygen O_2_ fraction (PaO_2_/FiO_2_) ≤ 150 with FiO_2_ of less than 0.6 and PEEP of at least 5 cm H_2_Ocontraindications to anticoagulation (i.e. any of the following: platelet count <50,000/mm^3^; international normalized ratio (INR) >1.5; stroke or severe head trauma or intracranial arterio-venous malformation, or cerebral aneurysm, or central nervous system mass lesion within the previous 3 months; epidural catheter in place or expected to be positioned during the study; history of congenital bleeding diathesis; gastrointestinal bleeding within the 6 weeks prior to study entry; esophageal varices, chronic jaundice, cirrhosis, or chronic ascites; trauma);heparin-induced thrombocytopeniabody weight >120 kgcontraindication to continuation of active treatmentfailure to obtain consentdifficult or impossible catheterization of femoral and jugular veinpneumothoraxsevere liver insufficiency (Child-Pugh scores >7) or fulminant hepatic failurediagnosis of acute or chronic neuromuscular diseasechronic mechanical ventilation prior to hospital admissionmoribund patientinclusion in other interventional trials

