#### Group B: Standard of care plus ECCO_2_R

NIV is applied and managed with the same modalities and at the same conditions as in Group A (standard of care).

After setting NIV, percutaneous vascular access is provided using a double lumen catheter inserted in the internal jugular vein or in the femoral vein (14F, Joline GmbH & Co. KG, Germany). An ECCO_2_R device will be used (DECAPsmart, Medica S.p.A.- Intensivecare s.r.l., Salerno, Italy). Blood flow is driven by a roller nonocclusive pump (0–450 mL/min) through a polymethylpentene artificial lung (priming volume, 200 mL; contact surface area, 0.8 m^2^; maximum blood flow rate, 450 mL/min) that is connected to a fresh gas flow source delivering 100% oxygen at a constant rate of 8 L/min. A starting dose of heparin (80 IU/kg bolus followed by ∼18 IU/kg/ hour infusion) will be delivered by using a syringe pump included in the system. Continuous infusion of heparin is hence titrated to maintain values of activated partial thromboplastin time (aPTT) in the range 35-80 sec or aPTT ratio of 1.5-2.0; aPTT is checked approximately every 2-3 hours during the first 6 hours from therapy initiation; afterwards, aPTT is checked every 6 hours. ECCO_2_R will be continued for at least 24 hours.

Intubation criteria are the same as in Group A (standard of care).

Weaning from ECCO_2_R must always precede weaning from mechanical ventilation. ECCO_2_R will be interrupted while keeping mechanical ventilation (invasive or non-invasive) when all of the following are achieved for at least 12 hours:
respiratory rate<25 breaths/min;pH>7.35;arterial PCO_2_<20% of the baseline value;absence of use of the accessory muscles or paradoxical abdominal movements.

Criteria to (a) *run formal assessment of discontinuation* from mechanical ventilation (invasive or non-invasive) through a daily spontaneous breathing trial (SBT); (b) to be defined as “weaned from mechanical ventilation” (invasive or non-invasive) are the same as in Group A (standard of care).

Use of ECCO_2_R is stopped and device (and catheter) removed in the following situations:
Air embolus in the extracorporeal circuitCircuit clotting leading to an abrupt stop of extracorporeal blood flowDevice malfunction leading to abrupt stop of extracorporeal blood flowSevere thrombocytopenia (< 29,000/mm^3^)Fibrinogen < 1g/L or fibrinogen < 1.5 g/L with diffuse bleedingAnytime the physician in charge believes that the protocol may be compromising patient’s outcome

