### Safety

Safety will be assessed by measuring the frequency of serious adverse events (SAE). A serious adverse event (SAE) in the trial is defined as:
any event that is fatal or immediately life threatening, permanently disabling, severely incapacitating or requires prolonged hospitalization **OR**any event that may jeopardize the patient and requires medical or surgical intervention to prevent one of the outcomes listed above **AND**which the attending physician perceives may be directly related to enrollment in the clinical trial.

Investigators will report severe adverse events to the clinical coordinator. An independent Data and Safety Monitoring Board (DSMB) will receive a detailed written report and evaluate whether the SAE is attributable to ECCO_2_R. SAE will be considered to be study-related if the event follows a reasonable sequence from a study procedure and could be produced by the study procedure. SAE will be considered not study related if they are thought to be primarily related to the underlying disease and its sequelae.

Other adverse events not fulfilling the above definition are recorded as ECCO_2_R related adverse events (ECCO_2_R-AE) and classified as:

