**mechanical**
difficulties upon catheter insertion (i.e. need for >2 attempts at catheter insertion during primary placement procedure);pump malfunction (i.e. need for >2 consecutive interventions during the same treatment with the same blood circuit, regardless of the need for stopping the procedure or for replacement of the pump);membrane lung clotting (leading to interruption of ECCO_2_R and/or circuit replacement);catheter displacement;cannula thrombosis;air in the circuit;tubing rupture;system leaks;**clinical**:
hemolysis (i.e. serum free hemoglobin ≥ 100 mg/L or hematocrit reduction not related to hemorrhage or other causes of blood loss, jaundice, hemoglobinuria, impaired renal function);bleeding (related to cannula insertion, and/or at cannula site; bleeding is considered “significant” if requires administration of ≥1 unit of packed red cells);hemodynamic instability (see criteria in the ‘Treatment of participants’ paragraph);ischemic/gangrenous bowel;pneumothorax;renal complications (i.e., occurrence of serum creatinine >1.5 mg/dl after initiation of ECCO_2_R);infectious complications (i.e., occurrence of culture-proven new infection after initiation of ECCO_2_R);thromboembolic complications (i.e., occurrence of deep venous thrombosis or pulmonary embolism after initiation of ECCO_2_R);thrombocytopenia (platelet count below 50,000/mm^3^);hypofibrinogenemia (i.e. fibrinogen < 1.5 g/L);neurologic complications (i.e. occurrence of cerebral infarction, or clinical seizure, or cerebral hemorrhage or cerebral edema after initiation of ECCO_2_R).

Each SAE will be notified by the investigator to the coordinating center, DSMB and ethics committee within 24 hours of occurrence. A detailed report will be sent by the investigator within 5 days of occurrence. The DSMB will examine every report immediately and will take every measure needed to ensure patients safety. Moreover, the DSMB will also meet every 30 enrolled patients to perform all necessary safety analyses. The DSMB can irrevocably halt the trial if the data analysis would show risks for patients’ safety.

An appropriate insurance policy, covering all enrolled patients for possible harm will be activated before enrollment of the first patient.

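### The bleeding class of the ECCO2R adverse events is limited to the cannula, so non-serious bleeding elsewhere under systemic heparin has no class or grade and bleeding can be understated

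*Protocol article*

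**What the plan says.** The Safety section works in two tiers. The first is the SAE, which covers "any event that is fatal or immediately life threatening, permanently disabling, severely incapacitating or requires prolonged hospitalization" and, as a second limb, events that may jeopardize the patient and need intervention to prevent such an outcome. A condition that the attending physician perceives a possible direct relation to enrollment follows. The second tier takes the remainder: "Other adverse events not fulfilling the above definition are recorded as ECCO_2_R related adverse events", to be sorted into a mechanical and a clinical list.

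The bleeding item of the clinical list reads "bleeding (related to cannula insertion, and/or at cannula site", and the same parenthesis grades bleeding as significant when at least 1 unit of packed red cells has to be given. The neurologic item of the same list covers "occurrence of cerebral infarction, or clinical seizure, or cerebral hemorrhage or cerebral edema after initiation of ECCO_2_R".

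On exposure, the Group B section sets out "A starting dose of heparin (80 IU/kg bolus followed by" an infusion, and then states: "Continuous infusion of heparin is hence titrated to maintain values of activated partial thromboplastin time (aPTT"). The exclusion criteria list, among contraindications to anticoagulation, "gastrointestinal bleeding within the 6 weeks prior to study entry". One of the Group B criteria for stopping ECCO2R combines low fibrinogen with diffuse bleeding.

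The Secondary outcomes section includes the incidence of adverse events as the Safety section defines them. The section on evaluation of secondary endpoints compares the rates of adverse and severe adverse events between arms with a chi-square test.

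**The concern.** The exposure is systemic but the outcome definition is local. Heparin given by bolus and titrated infusion can cause bleeding at any site, and the protocol's own exclusion and stopping criteria show that its authors expected this. The bleeding item nevertheless counts only what arises from cannula insertion or at the cannula site.

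The Discussion presents the trial as a weighing of avoided intubation against potentially serious complications of ECCO2R. A bleeding count that leaves out part of the bleeding under anticoagulation would make the harm side of that comparison look smaller than it is. The restriction cannot be put down to detail held in an analysis plan, because the secondary outcome points to this text for its definition.

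**Working it through.** The plan states no bleeding rate, so there is no figure to reproduce. The check is whether any other provision catches a bleed away from the cannula.

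**Step 1: other items of the clinical list.**
- Neurologic complications: catch cerebral hemorrhage, but under that heading and not as bleeding.
- Hemolysis: its hematocrit criterion expressly leaves out falls explained by hemorrhage.
- Hemodynamic instability: could catch a massive bleed, but not as bleeding.
- Hypofibrinogenemia: could catch the laboratory part of the stopping criterion, but not the diffuse bleeding that goes with it.
- Infectious and thromboembolic complications: neither is tied to the cannula. Bleeding is the only clinical item that is.
- Other events: no such item exists.

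**Step 2: the SAE route.** It does not depend on site, so a serious gastrointestinal bleed can enter. It has no bleeding category, however, so it does not yield a bleeding count. As printed, it is unclear whether the relatedness condition governs both limbs or only the second. If it governs both, a serious bleed that the physician does not perceive as related fails the SAE definition and drops to the second tier, where it has no bleeding class unless it is at the cannula. The trial is unblinded (Trial design), so that judgement is made with the arm known.

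**Step 3: the same event at two sites.** Take a bleed that needs 2 units of packed red cells and is not an SAE. At the cannula it is a bleeding event and graded significant. In the stomach it is in neither the class nor the grade.

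**Step 4: possible size, on assumed inputs only.** Let p be the true proportion of Group B patients with any bleeding, and s the share of those patients whose bleeds all fall outside the class. The counted proportion is p × (1 − s). Group B has 142 patients (Sample size).

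| Assumed p | Patients (142 × p) | Assumed s | Counted p × (1 − s) |
|---|---|---|---|
| 10% | 14.2 | 25% | 7.5% |
| 10% | 14.2 | 50% | 5.0% |
| 20% | 28.4 | 25% | 15.0% |
| 20% | 28.4 | 50% | 10.0% |
| any | 142 × p | 0% | p, nothing lost |

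Neither p nor s comes from the documents. The table shows only how the class count responds to the site restriction. It does not subtract bleeds that are reported as SAEs.

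**The case against.** The best defence is that the list is the residual tier. The Safety section says that safety is assessed by the frequency of SAEs, and these count at any site. Each is notified within 24 hours and goes to the DSMB. A transfused gastrointestinal bleed in an intensive care patient may well prolong the stay, or jeopardize the patient and need intervention, and so qualify. This stands: clinically serious bleeding is not lost to safety reporting. It does not supply a bleeding count, and it leaves the non-serious tier without a class.

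The Safety section also says that other events are recorded before they are classified, and nothing says that an event fitting no item is discarded. This stands too. What is shown is a fault in the bleeding class and its grade, not a proven loss from the overall adverse event incidence.

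A reader might go further in four ways, and the documents do not support these:
- That all bleeding away from the insertion site lacks a class. Cerebral hemorrhage has one, and because femoral access is allowed, a retroperitoneal bleed can count as related to cannula insertion.
- That the trial's bleeding rate will be too low. No separate bleeding rate is a named outcome, and the class falls short only if such bleeds occur.
- That most of the hazard of anticoagulation goes uncounted. No rate or site split is given. The figure of almost half of patients, quoted from the matched cohort study, concerns all ECCO2R complications.
- That DSMB review is impaired. The board examines every SAE report and performs all necessary safety analyses every 30 patients. Nothing confines it to the listed classes.

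Finally, the full protocol is not shown, so the absence of a location field here is no fault in itself. The restrictive wording is.

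**Conclusion.** The point holds for the bleeding class. Bleeding that is neither cannula-related nor cerebral, and that does not meet the SAE definition, has no class and no severity grade. Bleeding reported from this class can therefore understate bleeding under ECCO2R. Within Group B the omission can only lower the count. For a comparison between arms, the direction also depends on whether such bleeding is more frequent in Group B, which is plausible under heparin but not quantified in the documents.

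The size cannot be stated; it ranges from nothing upwards according to how many bleeds fall outside the class. The conclusion rests on the list being applied as printed. The primary endpoint and the sample size are not affected, and SAE reporting stays open to bleeds at any site.

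**What to change.** Define the item as bleeding at any site. Record the location (for example cannula, gastrointestinal, airway, intracranial, retroperitoneal, other). Apply the existing transfusion-based grade to every site, record the item alike in both arms, and report cannula-site bleeding as a subset so that the present definition can still be read off. State whether an intracranial bleed is shown under bleeding, under neurologic complications or under both, so that one event is not counted twice in a total.

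The cost is one definition and one eCRF field, with no added procedure and no change to treatment. The reported bleeding rate will be higher, or at least no lower. The Trial status section says that recruitment had not begun at the time of writing, when the change would be cheapest. Bleeds that are not recorded during enrollment may be hard to recover later.

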### Sample size

A two-sided log-rank test with an overall sample size of 284 subjects (142 in the control group and 142 in the treatment group) achieves 90% power at a 0.05 significance level to detect a hazard ratio of 0.67 when the proportion surviving without events in the control group is 40% (we estimated a combined proportion of death, prolonged mechanical ventilation, septic shock, severe hypoxemia and second episode of COPD exacerbation of 60% [23–33]). The study will last 25 months of which 24 months to accrual and 1 month of follow up. No subject will drop out of the control/treatment group. We assume no cases of switch (crossing-over) between the arms: the proportion of the control group that switches to a group with a risk rate equal to the treatment group is equal to zero (and vice versa).

This study has been designed to demonstrate a relative increase of 35% in the event free survival (from 40% to 54%), assuming the above-mentioned parameters.

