### Primary outcome

The primary outcome is event free survival, defined as survival at day 28 free of any of the following: (a) prolonged mechanical ventilation; (b) development of septic shock; (c) occurrence of severe hypoxemia; (d) occurrence of a second episode of COPD exacerbation (either or not requiring mechanical ventilation); (e) 28-day all cause death. By analyzing the relevant epidemiological literature on COPD exacerbations [23–33] and on their complications [34–37] we could determine that these five elements are the most common complications in hospitalized AECOPD patients.
**Prolonged mechanical ventilation** is defined as mechanical ventilation (invasive and non-invasive) applied for ≥ 14 days uninterrupted for more than 48 hours.**Septic shock** is defined by the presence of (a) sepsis (organ dysfunction caused by proven infection with an increase in the Sequential Organ Failure Assessment (SOFA) score of 2 points or more); (b) need for vasopressors to maintain a mean arterial pressure of 65 mmHg or greater; (c) serum lactate levels greater than 2 mmol/l (>18mg/dl) in the absence of hypovolemia.**Severe hypoxemia** is defined as occurrence of a ratio of arterial-to-inspired oxygen O_2_ fraction (PaO_2_/FiO_2_) ≤ 150 with FiO_2_ of less than 0.6 and PEEP of at least 5 cm H_2_O for at least 12 hours.**Second episode of COPD exacerbation** is defined as occurrence of sustained (≥24 h) increase in cough, sputum production, dyspnea and arterial pH≤7.30 (either or not requiring mechanical ventilation).**28-day all-cause mortality** is defined at 672 hours from randomization. All patients will be classified as either “alive at Study Day 28” or, if dead, “dead at Study Day 28.” For example, day zero is the day of randomization and day 1 is the next day and encompasses all events that occur midnight-to-midnight, etc.

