## Discussion

The consistency of the data from systematic reviews and matched cohort studies [12–14], and the observation of the continuous increase use of ECCO_2_R despite the lack of solid evidence [12] confirm that the equipoise regarding the use of ECCO_2_R justifies our randomized clinical trial to evaluate whether patients with respiratory acidosis refractory to NIV should be intubated and take the risks associated with invasive mechanical ventilation, or should be connected to ECCO_2_R to avoid intubation, but run the risk of the potentially serious ECCO_2_R-related complications. Moreover, this trial may allow clinicians and hospital managers to know whether this treatment should be made available or should be avoided since inappropriate and associated to serious side effects.

One possible limitation of our study design is that it doesn’t include long-term patient-centered outcome measures; however, we feel that long-term outcome measures would add complexity to our pragmatic trial design and should be investigated in future trials, especially after clear evidence on shorter-term efficacy and safety are gathered.

The ORION trial, owing to its pragmatic nature, planned sample size and composite primary outcome is expected to provide valuable and definite answers to these important research questions. Hypercapnic exacerbation of COPD represent a significant clinical (prognosis), social (quality of life) and economic (health-care costs) burden worldwide and the avoidance of invasive mechanical ventilation through the application of ECCO_2_R (combined with NIV) may significantly impact the natural history of COPD itself.

Presently, the interest of the scientific community for the subject is very high, and this work is thus potentially highly significant in the field of respiratory intensive care medicine.

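### With the endpoint fixed at day 28, 284 patients give about 69% power for a hazard ratio of 0.67, not the stated 90%: about 150 events are expected and about 262 are needed.

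*Protocol article*

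**What the plan says.** The Sample size section specifies "A two-sided log-rank test with an overall sample size of 284 subjects" ("142 in the control group and 142 in the treatment group"), which "achieves 90% power at a 0.05 significance level to detect a hazard ratio of 0.67 when the proportion surviving without events" is 40% in the control group. It describes the target as a rise in event-free survival from 40% to 54%, and assumes no dropout and no switching between arms. On timing it says: "The study will last 25 months of which 24 months to accrual and 1 month of follow up". It gives no number of events.

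The Primary outcome section fixes the horizon: "The primary outcome is event free survival, defined as survival at day 28 free of any of the following". It sets the mortality component at 672 hours from randomization, which is 28 days. The section on the trial hypothesis and main objective also defines event-free survival at day 28. The primary analysis is Kaplan-Meier estimation with a stratified log-rank test.

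**The concern.** The power of a log-rank test is governed by the number of events, not the number of patients. If about half the patients reach day 28 without an event, 284 patients cannot supply the events that 90% power requires at a hazard ratio of 0.67. The paragraph therefore appears to conflict with the endpoint it serves.

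The sample size was justified by this power figure. If the figure is wrong, the trial is about three times as likely as stated to miss the effect it was designed to find. The Discussion says that the trial, given its "planned sample size and composite primary outcome is expected to provide valuable and definite answers", will settle the question, and adds that it may tell clinicians whether the treatment should be avoided. A non-significant result would support that reading much less well at 69% power than at 90%.

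**Working it through.** **Inputs** (Sample size section unless noted): two-sided α = 0.05; 142 per arm; hazard ratio (HR) 0.67; control event-free proportion 40%; no dropout; no crossover; 24 months of accrual plus 1 month; endpoint at day 28 (Primary outcome section).

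**1. Are the effect figures consistent?** Under proportional hazards the treatment event-free proportion is 0.40^0.67 = 0.541, which matches the stated 54%. Working back from exactly 54%, HR = ln(0.54)/ln(0.40) = 0.6725. The effect is coherent; the question is the power.

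**2. Can the stated 90% be reproduced?** Approximately, if patients go on contributing events until a common study end at month 25. Take 40% as the one-month figure (an assumption; the paragraph names no time point), with constant hazards and uniform accrual over 24 months:

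- λ(control) = −ln(0.40) = 0.916 per month; λ(treatment) = 0.67 × 0.916 = 0.614.
- P(event) = 1 − (e^(−λ) − e^(−25λ)) / (24λ), which gives 0.982 and 0.963.
- Events = 142 × (0.982 + 0.963) ≈ 276.
- Power = 91.4% (Schoenfeld), 90.7% (Freedman), 90.9% (Lakatos), 91.2% (simulation).

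The stated power is thus recovered to within about 2 points, but only with patients followed well past day 28.

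**3. Events needed for 90% power at HR 0.67.** (1.960 + 1.2816)² = 10.507.

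- Schoenfeld: 4 × 10.507 / (ln 0.67)² = 4 × 10.507 / 0.4005² ≈ 262.
- Freedman: (1.67/0.33)² × 10.507 = 269.1, rounded up to 270.

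**4. Events expected with the day-28 endpoint.**

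- Control: 142 × 0.60 = 85.2.
- Treatment: 142 × (1 − 0.541) = 65.1.
- Total: 150.3.

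Reaching 262 events would need 262/284 = 92% of patients to have an event, against the planned 60% and 46%.

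**5. Power with 150.3 events.**

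| Method | Power |
|---|---|
| Schoenfeld: Φ(√(150.3/4) × 0.4005 − 1.960) = Φ(0.495) | 69.0% |
| Freedman: Φ(√150.3 × 0.33/1.67 − 1.960) | 67.8% |
| Lakatos | 68.7% |
| Simulated log-rank, 20,000 runs | 68.5% |
| Log-rank stratified over 20 equal centres | 68% |
| Day-28 proportions compared directly | 66–67% |

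Reading the test as one-sided at 0.05, which the text does not say, gives 79% (Schoenfeld) or 78% (Freedman).

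**6. What 284 patients can detect (Schoenfeld, day-28 endpoint).** 90% power at HR about 0.58 (40% vs 58.6%); 80% power at HR about 0.63 (40% vs 56%).

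**7. Patients needed for 90% power at HR 0.67.** The average event probability is 150.3/284 = 0.529. Then 262/0.529 ≈ 495 (Schoenfeld) and 270/0.529 ≈ 510 (Freedman).

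**The case against.** The strongest reply concerns the explanation rather than the shortfall. The paragraph names no software, gives no time point for the 40%, and never says that patients are followed for events to month 25; one month of follow-up fits a 28-day endpoint. Nor does the reconstruction in step 2 single out one set of inputs: placing the 40% at 1.5 months (Freedman) or 2 months (Schoenfeld) in the same model also returns about 284 patients for 90% power. This stands. How the 90% arose is an inference, and the finding does not need it.

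The 69% is also conditional on the planning inputs. With control event rates of 70% or 80% and the same HR, the Schoenfeld formula gives 76% or 82%. This stands too, although those rates are not the protocol's and still fall short of 90%.

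Two further points are fair. Twenty-four months of accrual plus one month for the last patient is a correct description of trial length. The Discussion's wording is aspiration, not a design property, and the planned hazard ratio with its confidence interval will show the precision achieved. These limit the edits required; they do not rescue the stated power. No reading with a 28-day horizon was found that reaches 90% on the protocol's inputs.

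**Conclusion.** The concern holds. On the protocol's own assumptions (40% vs 54% event-free at day 28, HR 0.67, two-sided 5%, no dropout, no crossover), the trial expects about 150 events and has about 69% power, with a range of 68–69% across log-rank methods. The type II error is about 31%, three times the stated 10%.

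The result does not depend on constant hazards: under proportional hazards, the event count at a fixed horizon follows from the day-28 proportions alone. It rests on reading 40% and 54% as day-28 proportions, which the endpoint definition requires. Dropout or crossover, both set to zero, would lower power further. The stated power should be corrected before it is relied on.

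**What to change.** Restate the Sample size paragraph with follow-up fixed at 28 days per patient and the expected number of events given. Either of these would be correct under the stated assumptions:

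- *284 patients (about 150 expected events by day 28) give about 69% power at two-sided 5% to detect a hazard ratio of 0.67 (40% vs 54% event-free).*
- *284 patients give 90% power at two-sided 5% to detect a hazard ratio of about 0.58 (40% vs 59% event-free).*

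Keep the 25-month sentence as a statement of trial duration, but make clear that it is not time over which a patient can contribute primary events. Softening the Discussion's expectation of definite answers is advisable but optional.

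Correcting the statement costs one reworded paragraph and a less favourable power figure; it needs no extra patients. It does expose a choice for the sponsor: accept about 69% power, justify a larger target effect, or enlarge the trial to about 495 to 510 patients to keep 90% at HR 0.67. The Trial status section says that recruitment had not begun at the time of writing, so on that status the choice could be made before enrolment.

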### Trial hypothesis and main objective

A recent matched cohort study [14] with historical control, compared “*NIV-plus- ECCO*_*2*_*R*” and “*NIV-only*” in patients at risk of NIV failure, and showed that (a) the hazard of being intubated was three times higher in patients treated with “*NIV-only*” than in patients treated with “NIV-*plus*- *ECCO*_*2*_*R*”; (b) hospital mortality was significantly lower in “NIV *plus* ECCO_2_R” than in “NIV-*only*” [8% (95% CI 1.0-26.0%) vs. 33% (95% CI 18.0-57.5%), respectively]. However, ECCO_2_R-related complications were observed in almost half of the patients. A recent systematic review [12] evaluated the efficacy and safety of ECCO_2_R in patients with hypercapnic respiratory failure across 12 studies and showed that the majority of patients were either successfully weaned from mechanical ventilation or sustained on NIV, avoiding intubation. However, this high success rate was associated with a high frequency of potentially severe complications [12].

Accordingly, the main objective of this randomized multicenter clinical trial is to test the hypothesis that in patients with acute life-threatening exacerbation of COPD, use of ECCO_2_R could increase event-free survival as compared to standard of care. Event free survival is defined as survival at day 28 free of septic shock, second episode of COPD exacerbation, occurrence of severe hypoxemia, and prolonged mechanical ventilation.

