Interruptions of ECCO_2_R (for any cause) lasting longer than 6 hours are to be considered ‘treatment failure’ and lead to termination of the experimental protocol.

All concomitant therapies foreseen by the standard of care of enrolled patients are allowed.

Post-trial care will be delivered according to the standard of care for AECOPD patients.

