### Sites and sites monitoring

The study will be conducted at up to twenty sites within Italy. Three site visits for each center will be performed (start of enrollment, mid-study, end of enrollment). Additional site visits will be performed as required. The coordinating center (University of Bologna – Policlinico S.Orsola-Malpighi) will supervise all aspects of the study and will be available to participant sites 24 hours, 7 days. All sites must have significant experience in treating AECOPD and with ECCO_2_R (i.e., all centers must routinely use continuous renal replacement therapy and perform at least 10 ECCO_2_R runs per year). Frequent investigators’ meeting will be planned in order to motivate enrollment. The coordinating center will provide logistic support to all participating sites in order to ensure efficient enrolment.

More specific data about sites can be obtained from the corresponding author.

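### The 90% power assumes that no Group B patient reverts to the control risk, although the protocol foresees early device removal; under ITT the stated figure is a best case

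*Protocol article*

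**What the plan says.** In the protocol article, Sample size, the calculation is introduced with "A two-sided log-rank test with an overall sample size of 284 subjects" ("142 in the control group and 142 in the treatment group"), which "achieves 90% power at a 0.05 significance level" for a hazard ratio of 0.67 with 40% event-free in the control arm. The same paragraph adds "We assume no cases of switch (crossing-over) between the arms". It explains a switch as taking on the risk rate of the other arm, and sets that proportion to zero each way.

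Under Group B, the text says "Use of ECCO_2_R is stopped and device (and catheter) removed in the following situations" and lists six of them: air embolus, circuit clotting, device malfunction, severe thrombocytopenia, low fibrinogen, and the physician's judgement that the protocol may be harming the patient. It then classes any interruption longer than 6 hours as treatment failure that ends the experimental protocol. NIV management and intubation criteria are the same as in Group A throughout.

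Statistical analysis makes ITT on all randomised patients the primary approach and plans exploratory as-treated analyses.

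**The concern.** The zero-switch condition is an explicit input to the 90%, so it is not a detail left to a later document. Elsewhere the protocol expects some Group B patients to come off ECCO2R for reasons other than successful weaning. From then on they receive the care described for Group A, while ITT keeps them in Group B. To the extent that they also take on the Group A risk, they are switches in the sense the Sample size section uses, and the hazard ratio moves towards 1.

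At stake is the reading of a near-null result. It would be set against a trial described as having 90% power for HR 0.67, when part of the shortfall could come from early loss of the device.

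**Working it through.** **Inputs from Sample size and Primary outcome.** 142 per arm; two-sided alpha 0.05; HR 0.67; control event-free proportion 0.40; 24 months of accrual plus 1 month of follow-up; outcome assessed at day 28; no dropout and no switching. Implied Group B event-free proportion: 0.40^0.67 = 0.541, which agrees with the stated 54%.

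**Events needed for 90% power.** Schoenfeld: 4 × (1.960 + 1.282)² / (ln 0.67)² = 263 after rounding up. Freedman: ((1.960 + 1.282) × 1.67/0.33)² = 270 after rounding up.

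**Reproducing 284 (model a).** Assume exponential hazards with 40% event-free at 1 month, uniform accrual, and every patient contributing events until study end.
- Hazards per month: control −ln 0.40 = 0.916; Group B 0.67 × 0.916 = 0.614.
- Event probability per arm: 1 − [e^(−λ) − e^(−25λ)]/(24λ), which gives 0.982 and 0.963, mean 0.973.
- Events from 284: 142 × (0.982 + 0.963) ≈ 276.
- Power: Schoenfeld Φ(½ × √276.2 × 0.4005 − 1.960) = Φ(1.368) = 91.4%; Freedman 90.7%; an interval-by-interval log-rank calculation of Lakatos type 90.8%.
- N for 90%: about 270 to 278.

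The stated figure therefore reproduces with zero switching, but only if patients contribute events for up to 25 months.

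**28-day endpoint (model b).** Events: 142 × (0.60 + 0.459) ≈ 150. Power: Φ(½ × √150.3 × 0.4005 − 1.960) ≈ 69% (Schoenfeld), 68% (Freedman), 68.5% (interval calculation), all with zero switching.

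**Adding reversion in Group B.** A share x of Group B carries the control hazard from randomisation. The documents give no value of x, so these are assumptions. Interval calculation, 284 patients:

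| x | Power, model a | Power, 28-day endpoint |
|---|---|---|
| 0 | 90.8% | 68.5% |
| 5% | 88.1% | 64.0% |
| 10% | 85.0% | 59.4% |
| 20% | 77.0% | 49.7% |

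**Hand check of the last column.** Group B event-free = (1 − x) × 0.541 + x × 0.40; HR = ln(that)/ln 0.40.
- x = 10%: 0.527, HR 0.699, events 142 × (0.60 + 0.473) ≈ 152, Schoenfeld power about 60%.
- x = 20%: 0.513, HR 0.728, events about 154, Schoenfeld power about 50%.

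Both agree with the table to within a point.

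**Scale in model a.** N for 90% power rises from about 277 to about 334 at x = 10% and about 412 at x = 20%.

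**The case against.** The strongest reply is that stopping the device is not switching arm. The device is meant to come off: at least 24 hours of treatment, then weaning. A patient who has had some ECCO2R need not acquire the control hazard, and HR 0.67 can be read as the ITT effect of a strategy that includes its own stop rules. This stands in part. It shows that the loss of power is not automatic and that reversion from randomisation is the worst case, since later removal dilutes less. But the article does not say that HR 0.67 is net of stopping, and it defines a switch by risk, so the point needs a sentence either way.

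Four stronger readings are tempting, and the documents do not support them.
- *The design contradicts the assumption.* Stop rules make some reversion likely, but they give no rate and do not say that risk reverts. Optimistic is the right word.
- *Patients leave the trial.* Those taken off the device stay in follow-up and in the ITT analysis, so the stop rules do not touch the zero-dropout statement.
- *About half will lose the device.* The Background says "ECCO_2_R-related complications were observed in almost half of the patients", but this is a complication rate in a historical-control cohort. Several adverse events listed under Safety need no removal, such as difficult catheter insertion.
- *Group A may receive ECCO2R.* One could infer this from "All concomitant therapies foreseen by the standard of care of enrolled patients are allowed" together with the requirement that sites "perform at least 10 ECCO_2_R runs per year". But the Background gives the standard of care as NIV followed by invasive ventilation, Group B is titled as standard of care plus ECCO2R, and the primary analysis compares NIV plus ECCO2R with NIV only. Site experience shows availability, not planned use in controls. The lack of an express ban is silence in a condensed article.

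The as-treated analyses will help in interpreting a null result, but they are exploratory and do not change the power of the primary test.

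**Conclusion.** The point holds as a matter of optimism. Zero reversion in Group B is at odds with the non-adherence the protocol itself foresees, so as far as this assumption goes 90% is an upper bound, unless HR 0.67 was already net of device stopping. In the model that reproduces 284, the cost is roughly 3, 6 and 14 points of power at 5, 10 and 20% reversion. These sizes rest on assumed shares, exponential hazards and worst-case timing.

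This is not the main weakness of the 90%. With no switching at all, the 28-day endpoint yields about 150 events and about 69% power. Reversion is a separate loss on top of that, to about 59% and 50% at 10% and 20%, and correcting the switching assumption alone would not restore 90%.

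**What to change.** In Sample size, do one of two things.
- Replace the zero-switch assumption for Group B by a stated range, for example 0 to 20% and labelled as an assumption, and restate the power of 284 patients over that range using the number of events expected by day 28.
- State that HR 0.67 is an ITT effect already net of device stopping, and give the basis for that.

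No change to the treatment or stop rules is needed for this point. The cost is a rerun of the power calculation and a few sentences, with no added patients. The drawback is a less favourable stated power. The article reports that recruitment had not begun, so the statement can be corrected before any data exist.
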